### Step 3: testing phase

The designed implementation strategies will be used to deploy the PCRPs in daily care and will be evaluated and compared on (A) effectiveness, (B) experiences of participants (process evaluation) and (C) costs. In all participating hospitals, the trial will be conducted for a half to 1 year, depending on the number of cancer patients per year in the participating hospitals allowing for fast accrual. Between 6 to 12 months after introduction of the implementation strategies, the outcomes of the PD and MF strategies will be evaluated and compared.

#### To test and compare both implementation strategies in terms of effectiveness

##### Study population

The study population in this evaluation will have the same characteristics as the study population in the ‘Analysis of the currently achieved implementation of PCRPs in daily care’ section.

##### Data collection

As described in the ‘Analysis of the currently achieved implementation of PCRPs in daily care’ section, quality indicators will be used to explore the actual achieved implementation of the PCRPs after the introduction of the developed implementation strategies. By comparing the implementation of PCRPs before and during the implementation period, we can evaluate the effectiveness of the strategies. The process of data collection of the quality indicators during the implementation period will be similar as the pre-measurement described in the ‘Analysis of the currently achieved implementation of PCRPs in daily care’ section.

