However, strategies aimed at professionals (educational outreach, audit and feedback) can also result in successful implementation (professional performance, patient outcomes and costs) [86, 87]. Strategies directed on the organization could support the implementation of PCRPs as well, mainly because contextual factors, such as workload, poor coordination and management, can be important barriers for success.

In our present study, we aim to identify the most effective strategy to implement PCRPs into daily care. Specific goals are to (1) gain insight into the specific features needed for a successful implementation by exploring the setting and factors (barriers and facilitators) that might influence the implementation of PCRPs. After this, (2) we aim to develop a patient-directed strategy and a multi-faceted strategy. The patient-directed strategy will be designed to embed the success of implementation of PCRPs by influencing the patients, and the multi-faceted strategy will be designed to embed the success by not only influencing the patients but also professionals and organizational aspects. Both strategies will be designed tailored to the setting and found factors affecting implementation. We also aim to (3) compare the effectiveness, experiences of participants (process evaluation) and costs of both strategies on the hospital and patient level and (4) get insight into the additional effects of strategies directed also at professionals and organization aspects compared to patient-only strategies.

Our first hypothesis is that hospitals with a multi-faceted strategy will have a more effective implementation of PCRPs in comparison with hospitals with a patient-directed strategy.

Our second hypothesis is that the patients and professionals will experience more positive experiences with the multi-faceted strategy in comparison with hospitals with a patient-directed strategy.

Our third hypothesis is that those hospitals with the multi-faceted strategy will have higher costs (incremental costs) in comparison with hospitals using the patient-directed strategy.

Our last hypothesis is that the incremental cost-effectiveness ratio (ICER) of the multi-faceted strategy will be lower than the patient-directed strategy.

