The results of the literature search will, together with the knowledge based on the results of the preparatory phase in step 1, be the basis to select and develop the implementation strategies during roundtable discussions. For the five hospitals of the PD-strategy group, a single-faceted patient-directed strategy will be designed that will embed the change only at the patient level. For the hospitals of the MF-strategy group, a multi-faceted strategy will be designed that will embed the change at the patient, professional and organizational levels. The MF strategy will consist also of the PD strategy, so the additional value of the strategies directed at the professional and organization can be evaluated afterwards. For the roundtable discussions, an expert panel will be composed consisting of representatives from the participating hospitals (patients, healthcare professionals and hospital managers), experts on cancer rehabilitation and experts on implementation science.

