##### Power calculation

A priori sample size calculations were based on the primary outcome measures, percentage of screened patients and percentage of referrals to PCRPs where needed. A power analysis for a comparison between the PD- and MF-strategy groups on the primary outcomes estimated a sample size of five hospitals per group (*n* = 50 patients per hospital) with a power of 0.80 and a two-tailed alpha of 0.05 and accounting for an estimated dropout of 10 %. Specifically, to detect an effect size of 50 % in the MF-strategy group and of 20 % in the PD-strategy group.

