##### Planned analytic approach

Both univariate and multivariate (multi-level) analyses will be performed to obtain an indication of the effectiveness of the implementation strategies in increasing the proportion of patients who are treated according to the programme before and after applying the implementation strategy. In this analysis, adherence to the quality indicators will be used as dependent variables and patient characteristics (e.g. age, cancer type, clinical stage, co-morbidity, performance status and types of therapy) will be included as possible confounders. The results of the ‘post-measurement’ will be compared with the ‘pre-measurement’ . Additionally, the differences of the pre-post-measurements will be compared between the PD- and MF-strategy groups.

If possible, all outcomes (effectiveness, experiences of participants (process evaluation) and costs) will be analysed at the patient level (all patients of hospital PD strategy vs. all patients of hospital MF strategy). Additionally, we will analyse at the hospital level to explore the effects of the strategies related to hospital characteristics (university, teaching and non-teaching hospitals).

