An important limitation of our study is the absence of a proper randomized study design. This would eliminate bias in implementation strategy assignment and improve the evidence that differences in outcomes between the implementation strategies indicate significant effects on physical cancer rehabilitation care [125]. It is, however, also known that comparing complex interventions and programmes is a challenging matter, for which one has to settle with less advanced designs.

Our implementation strategies have the disadvantage of measuring the effect of the entire package of interventions, which might make it hard to distinguish which intervention was most effective regarding improved cancer rehabilitation care (with indicator adherence as effect measure). During the evaluation, we will try to get insight into the effect of each separate intervention by acquiring information from participants concerning the exposure to, use of and experiences with the different interventions.

A dilution of treatment effect could occur if patients participate in a PCRP themselves or when professionals and organizations use their own implementation strategies to achieve proper implementation. Local initiatives to optimize cancer rehabilitation during the intervention period might bias our study results. Therefore, information on local, non-study-related interventions will be additionally acquired during the process evaluation.

Hospitals, which agree to participate in our study, are probably committed to improve their quality of cancer rehabilitation care and the implementation of PCRPs. Their results will be generalizable for hospitals motivated to implement PCRPs. For hospitals less committed to achieve this goal, the outcomes might be less generalizable.

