## Conclusion

Our study is intended to highlight the important role of the right implementation strategy to provide evidence-based PCRPs to the patients. We believe that strategies tailored to the current setting and barriers and facilitators found will optimize the success of implementation of PCRPs. If one or both implementation strategies prove to be effective, the knowledge about the effectiveness, feasibility and cost of the tailored implementation strategies can help to apply these PCRPs successfully in the Dutch and other healthcare systems. Additionally, our study might give insight in the additional effects of strategies directed at patients, professionals and organizations in an implementation strategy for PCRPs. Finally, if the implementation strategies are effective, this will lead to improved survivorship care leading to better quality of life for cancer survivors.

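### Effectiveness is partly to be read from before-after change within each arm, and a conclusion that one or both strategies work is foreseen, but with no strategy-free arm the design supports only the MF-minus-PD contrast

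*Protocol article*

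**What the plan says.** All references are to the protocol article.

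- **Step 3, effectiveness, Data collection:** "By comparing the implementation of PCRPs before and during the implementation period, we can evaluate the effectiveness of the strategies". No comparator is mentioned in this sentence.
- **Step 3, effectiveness, Planned analytic approach:** the post-measurement results "will be compared with the ‘pre-measurement". The between-arm step follows: "Additionally, the differences of the pre-post-measurements will be compared between the PD- and MF-strategy groups".
- **Conclusion:** the benefits of the study are introduced with "If one or both implementation strategies prove to be effective".
- **Step 2:** "For the five hospitals of the PD-strategy group, a single-faceted patient-directed strategy will be designed". The same section says that the MF strategy also includes the PD strategy, so that the extra value of its other elements can be evaluated. No hospital is without a strategy.
- **Background, first hypothesis:** "hospitals with a multi-faceted strategy will have a more effective implementation of PCRPs in comparison with hospitals with a patient-directed strategy". The Abstract states the aim in the same terms, as the added value of MF over PD.
- **Power calculation:** "A power analysis for a comparison between the PD- and MF-strategy groups on the primary outcomes estimated a sample size of five hospitals per group".
- **Discussion:** "Local initiatives to optimize cancer rehabilitation during the intervention period might bias our study results". The remedy given is to collect information on such initiatives during the process evaluation. The absence of randomization is also conceded.

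**The concern.** The study has one controlled contrast, the change in MF hospitals minus the change in PD hospitals. It answers one question: do the professional and organizational elements add anything to the patient-directed strategy? Two statements go further. The Data collection sentence treats before-versus-during change as sufficient to judge the strategies, and the Conclusion allows a verdict on each strategy separately. Both need a comparison with hospitals that had no strategy, and there are none.

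At stake is what the trial may claim. If screening and referral rise everywhere for outside reasons, the text as written permits a statement that PD, MF or both are effective, even when the first hypothesis fails. The article names the MF-versus-PD comparison in its aim, hypothesis and sample size, but the effectiveness text does not say that this contrast decides the result.

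**Working it through.** **1. What each contrast identifies.** Let T be the change over time without any strategy, P the effect of the patient-directed strategy, and X the extra effect of the professional and organizational elements given on top of it.

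- PD arm, post minus pre: T(PD) + P
- MF arm, post minus pre: T(MF) + P + X
- Difference between the arms: X + [T(MF) − T(PD)]

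Neither within-arm change separates P from T. In the between-arm difference P cancels, and X is identified if T is the same in both arms. No contrast in the design isolates P, or P + X.

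**2. What the sample size was built for.** Stated inputs (Power calculation): 50 % versus 20 %, power 0.80, two-sided alpha 0.05, 10 % dropout, 5 hospitals × 50 = 250 patients per group. No intracluster correlation (ICC) is given, so the figure cannot be reproduced from stated inputs alone.

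- Independent patients: n = [1.96·√(2×0.35×0.65) + 0.842·√(0.25+0.16)]² / 0.30² = 38.5, so 39 per group (45 with continuity correction).
- Evaluable patients: 250 × 0.9 = 225 per group, 45 per hospital.
- Implied design effect: 225/39 = 5.77 or 225/45 = 5.0.
- Implied ICC, (design effect − 1)/44: 0.108 or 0.091.

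The stated size is thus attainable at an ICC of about 0.09 to 0.11, for PD versus MF. It was not derived for within-arm change.

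**3. Within-arm test under a pure time trend, patients treated as independent.** Assumptions: no strategy effect, n = 225 before and 225 after in one arm, different patients in the two periods. The baselines and rises are assumed, since the article gives none.

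Power = Φ{[δ − 1.96·√(2p̄(1−p̄)/n)] / √([p₀(1−p₀)+p₁(1−p₁)]/n)}

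- 20 % to 30 %: (0.10 − 1.96×0.04082)/0.04055 = 0.493, so Φ = 0.689
- 20 % to 25 %: 0.245
- 10 % to 20 %: 0.846

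**4. The same question at hospital level.** Simulation with 20,000 replicates: 5 hospitals per arm, 45 patients before and 45 after in each, no strategy effect, the same trend in both arms. Assumed logit-scale standard deviations are 0.4 between hospitals and 0.25 for hospital-by-period. Tests are t-tests on hospital changes, with 4 df within an arm and 8 df between arms.

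| Baseline | Assumed rise (points) | One given arm significant upward | At least one arm | Between-arm test of changes |
|---|---|---|---|---|
| 20 % | 0 | 0.023 | 0.045 | 0.050 |
| 20 % | 5 | 0.116 | 0.224 | 0.048 |
| 20 % | 10 | 0.318 | 0.532 | 0.049 |
| 20 % | 15 | 0.568 | 0.813 | 0.048 |
| 20 % | 20 | 0.778 | 0.950 | 0.050 |
| 10 % | 10 | 0.455 | 0.706 | 0.050 |
| 30 % | 10 | 0.257 | 0.454 | 0.052 |

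Allowing for clustering lowers the within-arm error but does not remove it. The between-arm test holds its level in every scenario because the trend was set equal in both arms.

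**The case against.** The strongest reply is that the article is plainly a study of MF versus PD. Its aim, first hypothesis, design statement and only power calculation say so, and the difference in pre-post change is already planned. The word that introduces that comparison can be read as sequence: changes are estimated first and then compared. The Data collection sentence explains why indicators are measured twice and does not exclude a comparison between arms. The analysis section claims only an indication of effectiveness. The ranking of contrasts may sit in an analysis plan that is not shown.

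Most of this stands, and it limits the point. A reader might infer that the between-arm contrast is a mere extra. The aim, hypothesis and sample size contradict that. A reader might also infer that a false claim of effectiveness would follow. That depends on a background rise for which the article gives no figure. Nor does the article support adding regression to the mean, since hospitals are not selected for poor baseline performance. It does not describe the national guideline or the parent programme as competing influences; only local initiatives are named as a source of bias.

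The 69 % ignores clustering, whereas multi-level analysis is planned. It also does not carry over directly to the referral outcome, which counts only patients who need referral and so has a smaller denominator.

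The reply does not answer the two explicit statements. Before-versus-during change is said to allow evaluation of the strategies, and a conclusion on one or both is foreseen. These are written inferences, not details left for later, and the design cannot deliver them.

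**Conclusion.** The point holds as a mismatch between stated inference and design. Within-arm change is uncontrolled, PD's own effect is not identified, and a claim that one or both strategies are effective would have to rest on that uncontrolled change. The controlled contrast exists, is planned and matches the hypothesis; it needs to be given the deciding role.

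The size is illustrative. For an assumed rise from 20 % to 30 % without any strategy effect, a within-arm test is significant in about 69 % of trials with independent patients. At hospital level, at least one arm is significant in about 53 %, and this runs from 22 % to 95 % for rises of 5 to 20 points from the same baseline. These figures rest on assumed trends and, at hospital level, on assumed variances. The roughly 5 % for the between-arm test holds only for a trend common to both arms. Since hospitals are not randomized, a trend that differs between arms would bias that contrast too.

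**What to change.** - In the effectiveness analysis, name the difference in pre-post change (MF minus PD) as the primary analysis for the first hypothesis, and label within-arm pre-post changes descriptive.
- Reword the Data collection sentence and the Conclusion so that they claim only what the contrast shows: whether professional and organizational elements improve screening and referral beyond the patient-directed strategy.
- Add to the limitations that this contrast is protected only against a trend common to both non-randomized arms.

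This costs text only: no extra hospitals, patients or measurements. According to Trial status, no indicator data had been gathered at submission, so at that stage the contrast could still be fixed in advance. The price is that the study gives up a confirmatory claim on PD alone, or on MF against no strategy, which the design cannot support anyway.

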##### Study outcomes

The primary outcome measures are two quality indicators: (A) the percentage of screened patients with the screening tool recommended by the Dutch guideline ‘Cancer Rehabilitation’ and (B) the percentage of referrals to PCRPs where needed, according to the Dutch guideline ‘Cancer Rehabilitation’.

Secondary outcome measures are the differences in adherence between the pre- and post-measurement to the remaining quality indicators (process and structure indicators) extracted from the Dutch guideline ‘Cancer Rehabilitation’ and often-used outcome indicators as QoL and patient empowerment.

##### Power calculation

A priori sample size calculations were based on the primary outcome measures, percentage of screened patients and percentage of referrals to PCRPs where needed. A power analysis for a comparison between the PD- and MF-strategy groups on the primary outcomes estimated a sample size of five hospitals per group (*n* = 50 patients per hospital) with a power of 0.80 and a two-tailed alpha of 0.05 and accounting for an estimated dropout of 10 %. Specifically, to detect an effect size of 50 % in the MF-strategy group and of 20 % in the PD-strategy group.

##### Planned analytic approach

Both univariate and multivariate (multi-level) analyses will be performed to obtain an indication of the effectiveness of the implementation strategies in increasing the proportion of patients who are treated according to the programme before and after applying the implementation strategy. In this analysis, adherence to the quality indicators will be used as dependent variables and patient characteristics (e.g. age, cancer type, clinical stage, co-morbidity, performance status and types of therapy) will be included as possible confounders. The results of the ‘post-measurement’ will be compared with the ‘pre-measurement’ . Additionally, the differences of the pre-post-measurements will be compared between the PD- and MF-strategy groups.

If possible, all outcomes (effectiveness, experiences of participants (process evaluation) and costs) will be analysed at the patient level (all patients of hospital PD strategy vs. all patients of hospital MF strategy). Additionally, we will analyse at the hospital level to explore the effects of the strategies related to hospital characteristics (university, teaching and non-teaching hospitals).

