**Fig. 1. Fig1:**
[figure not shown]
Overview of the planned stepwise approach of the study

In *step 1*, we will first analyse the currently achieved implementation of PCRPs in daily care and examine the factors (barriers and facilitators) that might influence optimal implementation of PCRPs. In *step 2*, we will use the background information of step 1 and a literature study to develop and tailor implementation strategies to the target group, the setting and the barriers to change. In *step 3*, we will then compare newly achieved implementation with the implementation measurements from step 1 to assess and compare the effectiveness of the two implementation strategies by a CBA design. We will also conduct a process evaluation and cost analysis. Clustering of the CBA study will be on the hospital level as matched pairs in a 1:1 ratio. The hospitals are situated in different regions in the Netherlands, and hospitals will be stratified by the study group, according to type of hospital (university, teaching and non-teaching hospitals) and capacity (number of beds).

Each group will contain one university, two teaching and two non-teaching hospitals in the Netherlands.

During our study, healthcare professionals of the participating hospitals will hand out patient information and informed consent to all eligible patients. Patients that give informed consent will be approached, screened and if eligible included as participant for one or more analyses of our study.

Professionals are asked for participation by writing. Professionals that give informed consent will be screened and if eligible included as a professional participant for one or more analyses of our study.

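### The effectiveness analysis does not make the clustered analysis decisive: univariate and all-patients comparisons stand beside the multi-level one, although strategy is allocated to five against five hospitals

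*Protocol article*

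**What the plan says.** The Design section makes the hospital the unit of allocation: "Clustering of the CBA study will be on the hospital level as matched pairs in a 1:1 ratio". Each group has five hospitals.

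The Planned analytic approach for effectiveness (Step 3) then sets out four things:

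- Two kinds of analysis side by side: "Both univariate and multivariate (multi-level) analyses will be performed to obtain an indication of the effectiveness". Patient characteristics enter as possible confounders.
- The contrasts: post against pre, and then the pre-post differences compared between the PD and MF groups.
- The level: where possible, all outcomes (effectiveness, experiences and costs) "will be analysed at the patient level (all patients of hospital PD strategy vs. all patients of hospital MF strategy").
- An additional hospital-level analysis, which explores how effects relate to hospital type (university, teaching, non-teaching).

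No sentence says which analysis decides on the two primary outcomes, or that hospital remains a term in the patient-level comparison.

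**The concern.** Screening and referral are largely hospital practices, so patients of one hospital resemble each other on these outcomes. The information on MF against PD comes from ten hospitals, not from 500 independent patients. A univariate test as ordinarily run takes the patients as independent. So does a comparison of all PD with all MF patients, unless hospital is kept in the model.

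Because the section gives the two kinds of analysis equal standing, a significant univariate result could be reported as the trial's answer even where the multi-level model does not support it. A difference that reflects only ordinary variation between hospitals could then be credited to the MF strategy. The hospital-level analysis does not protect against this, because its stated purpose is exploration by hospital type and not a test of the strategy.

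**Working it through.** **Inputs from the Power calculation section.** The test is at a "two-tailed alpha of 0.05" "with a power of 0.80". The calculation "estimated a sample size of five hospitals per group" with "50 patients per hospital" and 10 % dropout. It is meant "to detect an effect size of 50 % in the MF-strategy group and of 20 % in the PD-strategy group", read here as proportions. Analysed per hospital: m = 50 × 0.9 = 45, so 225 per group.

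**Assumed inputs.** The article gives no ICC and no correlation r between a hospital's pre and post levels. Ranges are used: ICC 0.02 to 0.11 and r 0.5 to 0.9. Pre and post samples are taken as different patients.

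**The plan's own figure.** For 50 % against 20 %, independent patients would require 39 per group, or 45 with continuity correction. After dropout this is 44 or 50. Neither is 250. The planned size gives 80 % power only with an ICC of about 0.11: the design effect is 1 + 44 × 0.11 = 5.84, and 39 × 5.84 = 228, close to the 225 analysed. With a t reference on 8 df the matching ICC is about 0.09. The article does not state this ICC; 0.11 serves only as the upper end of the range.

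**Post-only comparison that ignores hospital.** The true variance exceeds the assumed one by DE = 1 + (m − 1) × ICC. The true error at nominal 5 % is 2 × [1 − Φ(1.96/√DE)].

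| ICC | DE | 1.96/√DE | true error |
|---|---|---|---|
| 0.02 | 1.88 | 1.43 | 15 % |
| 0.05 | 3.20 | 1.10 | 27 % |
| 0.11 | 5.84 | 0.81 | 42 % |

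A beta-binomial simulation (5 against 5 hospitals, m = 45, rate 20 %, 40,000 runs) gave 15.1 %, 27.4 % and 42.2 %.

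**Pre-post contrast that ignores hospital.** This is the between-group contrast that the article names. Stable hospital differences cancel, and only the part that changes between periods remains. With outcome variance v, a hospital's change has variance 2 × [ICC × v × (1 − r) + (1 − ICC) × v/m]. A test that ignores hospital assumes 2v/m. The ratio is DE = (1 − ICC) + m × ICC × (1 − r).

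| ICC | r | DE | 1.96/√DE | true error |
|---|---|---|---|---|
| 0.02 | 0.9 | 0.98 + 0.09 = 1.07 | 1.89 | 6 % |
| 0.05 | 0.8 | 0.95 + 0.45 = 1.40 | 1.66 | 10 % |
| 0.11 | 0.5 | 0.89 + 2.475 = 3.365 | 1.07 | 28.5 % |

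**Does a clustered test hold its level?** In simulation with 50 per hospital and ICC 0.01 to 0.20, an unpaired t-test on post-measurement hospital proportions (8 df) rejected in 4.6 to 5.2 % of runs. Its power for 50 % against 20 %, post-only with 45 per hospital, is 0.99 at ICC 0.02, 0.93 at 0.05 and 0.76 at 0.10.

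**Degrees of freedom.** Ten hospitals in two unpaired groups leave 10 − 2 = 8 df. Five matched pairs leave 5 − 1 = 4 df. The article announces matched pairs but does not say whether the analysis keeps them.

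**The case against.** The strongest reply is that the multi-level analysis is already in the plan, and the Design section names the hospital as the cluster. A multi-level model also uses patient-level observations, so the patient level may mean no more than the unit of observation within that model. The clause about feasibility may refer to data availability, since structure indicators exist only per hospital. A sample size that fits an ICC near 0.11 also suggests that the planners allowed for clustering, which sits badly with an intention to ignore it later. Random-effect structure and degrees of freedom are commonly left to the analysis plan.

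Most of this stands. A reader might infer that the article prescribes a pooled test without hospital for every outcome and that the false-positive rate is therefore several-fold too high. The text does not support that:

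- No sentence says that hospital is dropped.
- The process evaluation is descriptive and has no test.
- The cost section states no test and no confidence interval, so one cannot say that its intervals are too narrow.
- The large error rates belong mainly to a post-only comparison. For the named pre-post contrast the excess can be slight.
- The article states no reference distribution for the multi-level model, so it cannot be charged with using the wrong one.

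What the reply does not remove is the missing order of precedence. Univariate and multi-level analyses are placed on the same footing, and the only hospital-level analysis described has another purpose.

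**Conclusion.** The point holds as an unresolved choice that the text itself creates. The article announces two kinds of analysis, of which one ignores the unit of allocation as ordinarily run, and makes neither decisive. For the planned pre-post contrast, a test without hospital would have a true error between about 6 % and 28.5 % in the cases shown. For a post-only comparison it would be 15 % to 42 %. These figures rest on assumed ICCs and pre/post correlations, 45 analysed patients per hospital, equal cluster sizes and a normal approximation. The direction is robust: with any positive ICC a post-only test that ignores hospital exceeds 5 %, and so does the pre-post test whenever m × (1 − r) > 1, that is r below about 0.98 at m = 45. The size for this trial cannot be known from the article.

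**What to change.** In the Planned analytic approach for effectiveness:

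1. Name one main analysis for the two primary outcomes. This can be the arm-by-period contrast from the multi-level model, with random hospital and hospital-by-period effects and a small-sample degrees-of-freedom correction for ten clusters. An equivalent comparison of the ten hospital-level changes would also serve.
2. State whether the matched pairs of the Design section are kept in that analysis (4 df) or not (8 df).
3. State that every patient-level comparison of PD with MF keeps hospital in the model.
4. Label univariate results descriptive. They need not be deleted.
5. If uncertainty is reported for costs or ICERs, resample by hospital.

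The cost is wording and wider intervals, widest if the pairs are kept. No new data are needed. According to the Trial status section, quality-indicator data had not been gathered at submission, so the choice could be fixed before outcomes were seen.
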